## Abstract

**Background:**

The racial/ethnic and gender disparities in cardiovascular disease (CVD) morbidity and mortality in the United States are evident. Across nearly every metric, non-Hispanic Black women have poorer overall cardiovascular health. Emerging evidence shows a disproportionately high burden of increased CVD risk factors in Black women of childbearing age, which has a far-reaching impact on both maternal and child outcomes, resulting in premature onset of CVD and further widens the racial disparities in CVD. There is growing recognition that the fundamental driver of persistent racial/ethnic disparities in CVD, as well as disparities in behavioral risk factors such as physical activity and sleep, is structural racism. Further, the lived personal experience of racial discrimination not only has a negative impact on health behaviors, but also links to various physiological pathways to CVD risks, such as internalized stress resulting in a pro-inflammatory state. Limited research, however, has examined the interaction between daily experience and health behaviors, which are influenced by upstream social determinants of health, and the downstream effect on biological/physiological indicators of cardiovascular health in non-pregnant Black women of childbearing age.

**Methods/Design:**

The BLOOM Study is an observational study that combines real-time ambulatory assessments over a 10-day monitoring period with in-depth cross-sectional lab-based physiological and biological assessments. We will use a wrist-worn actigraphy device to capture 24-h movement behaviors and electronic ecological momentary assessment to capture perceived discrimination, microaggression, and stress. Blood pressure will be captured continuously through a wristband. Saliva samples will be self-collected to assess cortisol level as a biomarker of psychological stress. Lab assessments include a fasting venous blood sample, and assessment of various indices of peripheral and cerebral vascular function/health. Participants’ address or primary residence will be used to obtain neighborhood-level built environmental and social environmental characteristics. We plan to enroll 80 healthy Black women who are between 18 and 49 years old for this study.

**Discussion:**

Results from this study will inform the development of multilevel (i.e., individual, interpersonal, and social-environmental levels) lifestyle interventions tailored to Black women based on their lived experiences with the goal of reducing CVD risk.

**ClinicalTrials.gov Identifier:**

NCT06150989.

**Supplementary Information:**

The online version contains supplementary material available at 10.1186/s12905-024-03182-0.

## Introduction

In the United States, the prevalence of CVD risk factors (e.g., hypertension and diabetes mellitus) among women of childbearing age (18–49 years) has increased substantially over the last two decades [1]. Compared to non-Hispanic White women, non-Hispanic Black women (hereafter referred to as Black women) are more likely to have comorbid hypertension and diabetes, and more likely to have these comorbidities undiagnosed [2]. In addition to traditional CVD risk factors, adverse health behaviors, such as physical inactivity, insufficient sleep and poor-quality sleep, are recognized as modifiable factors that contribute to CVD disparities in Black Americans [3]. Compared to other racial/ethnic groups, Black women are less likely to report getting the recommended levels of physical activity [4], and report a higher prevalence of shorter sleep, having trouble falling asleep, trouble staying asleep, and not waking up most days feeling rested (≥ 4 in the previous week) [5]. There is an increasing interest in investigating the combined effects of 24-h movement behaviors on health [6]. From a movement perspective, the 24-h period is distributed among sleep, sedentary behavior, and physical activity. The time reallocation between sleep, sedentary behavior, and physical activity is associated with a number of health outcomes, such as physiologically relevant reductions in mortality risk and negative cardiometabolic biomarkers [7]. Thus, from a lifestyle intervention perspective, it is imperative to consider and target the three 24-h movement behaviors to optimally decrease CVD risk and maximize health benefits. The 24-hr movement guidelines outline recommendations for physical activity, sedentary behavior, and sleep based on empirical evidence [8]. Emerging evidence shows that this guideline adherence was lower in females than males; and lowest among non-Hispanic Blacks compared to other racial groups [9]. With these consideration in mind, this study is focused on physical activity, sedentary behavior, and sleep as key daily modifiable health behaviors.

It is widely recognized that the fundamental driver of persistent racial/ethnic disparities in CVD is structural racism [10]. Structural racism refers to the totality of ways in which society fosters racial discrimination through mutually reinforcing systems of housing, education, employment, healthcare, and other social determinants of health (SDOH) [10, 11]. Structural racism creates stressful and unhealthy social and built environments, which contributes to disparate behavioral risk factors such as physical inactivity and inadequate sleep among Black women [10, 12]. Several social and structural factors are associated with lower levels of physical activity among Black women [13], such as residential racial segregation resulting in communities with fewer physical characteristics that promote physical activity [14, 15], perceived time availability and monetary cost of exercise facilities, family/caregiving responsibilities, lack of physical activity partner or role models [16]. Similarly, decades of sleep disparities research indicates that several neighborhood and environmental factors, such as residential racial segregation (which can transcend socioeconomic status), and neighborhood ambient features of urban environments, such as loud noises or bright lights, can be deleterious to sleep [17].

In addition to impacting the social and built environments, systematic inequality also creates social stress from experience of racial discrimination and microaggressions. This type of social stress has been associated with unhealthy behaviors and may provoke severe psychological and physiological responses that lead to poor health outcomes [18–20]. For example, self-reported experiences of racial discrimination have been associated with shorter sleep duration [21] and increased sedentary time [22] among Black women. There are several known physiological pathways that link racism and racial discrimination to CVD risks, such as abnormal activation of the sympathetic nervous system from internalized stress, resulting in the augmented release of cortisol [23]. Previous studies have also shown an association between perceived discrimination and inflammatory markers such as high C-reactive protein (CRP) and interleukin-6 (IL-6) levels [20, 24]. Ultimately, constant psychological stress from adverse social conditions can cause biological responses (i.e., allostasis), which, over time, can cause neurohormonal imbalances, including augmented systemic inflammation and oxidative stress (i.e., allostatic overload) [25, 26]. These alterations can subsequently impair vascular function and responsiveness [27–29], which is an early indicator of atherogenesis and CVD risk [30].

Overall, previous work has shown evidence of how neighborhood-level characteristics could impact individual behaviors and suggested a link between social stress and CVD risk. However, limited studies have focused on how an individual’s *actual experiences and behaviors in their everyday life* may contribute to validated, measurable, and quantifiable biomarkers of CVD risk. This knowledge gap is particularly critical for effective lifestyle intervention development, because in order to promote sustainable behavioral change, a lifestyle intervention will need to consider the everyday contexts of a person’s life in the real-world setting. Accordingly, this observational study aims to: (1) Examine the impact of daily experience (i.e., racial discrimination, affective states, stress) on health behaviors (i.e., physical activity, sedentary behavior, sleep) at the intrapersonal level among Black women. We hypothesize that there is an acute positive association between negative daily experiences and unhealthy behaviors, i.e., a higher level of stress will lead to more time spent in sedentary behaviors that day and poorer sleep at night. (2) Test the association between daily behaviors and impairments in biomarkers associated with vascular function/health (i.e., augmented systemic inflammation and oxidative stress, impaired peripheral/cerebral vascular function, increased large artery stiffness), as well as the impact of daily experience on the relationship between behaviors and vascular function. We hypothesize that unhealthy behaviors are positively associated with vascular function impairments, and daily experiences moderate this association, i.e., negative daily experiences will augment the negative impact of unhealthy behaviors on vascular function. (3) Explore the influence of neighborhood-level characteristics (i.e., social environment factors: i.e., neighborhood income and poverty, racial composition; and built environment context, such as park density and walkability) on daily experience and health behaviors. We hypothesize that unfavorable neighborhood characteristics are associated with unhealthy daily behaviors and negative daily experiences. Figure 1 outlines the study’s conceptual diagram.

**Fig. 1 Fig1:**
[figure not shown]
Conceptual diagram by study aims and measures

## Methods

### Participants recruitment and eligibility

Black women (*n* = 80) will be recruited from the Dallas-Fort Worth Metroplex (Black residents make the 3rd largest racial group in this area). The research team will collaborate with local organizations, including the Tarrant County Health Equity Alliance [31], to assist with recruitment efforts. Study information will be shared at community events, newsletters, and email listservs. The research team will also apply strategies previously identified by scholars with expertise in recruitment and collaboration with Black women [32–34]. Participants can also be recruited from the University of Texas at Arlington (UTA) campus (e.g., students and staff) and through focused social media advertisement (e.g., filtered by geographic location, age, gender).

Interested women will complete a brief online screener to determine eligibility. To be eligible, participants must be assigned female at birth; between 18 and 49 years old; self-identify as Black or African American; not currently pregnant; ownership of a smartphone; and able to speak and read English. *Exclusion criteria* include diagnosed hypertension, cardiovascular, respiratory, metabolic, and/or neurological disorders; functional limitations or health issues that preclude physical activity; currently taking medications for thyroid function or psychological conditions such as depression, anxiety, and mood disorders; current use of oral or inhalant corticosteroids for asthma; or have regularly smoked within the last 2 years.

Recruitment for the study started in February 2024. The first study participant was enrolled on March 4th, 2024. As of May 2024, a total of 63 women completed the eligibility screener, and 27 of them were eligible for the study. Among women who were not eligible for the study, main reason was their current medication use (*n* = 15), followed by medical conditions (*n* = 12) and smoking status (*n* = 4). This study is currently enrolling participants, and we expect to finish study enrollment around October 2025.

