### Lab-based assessments (procedures and measures)

The following assessments of cardiovascular health indicators will take place during participants’ in-person study visit.

A fasting venous blood sample will be taken for assessment of a comprehensive metabolic panel (e.g., glucose, glycated hemoglobin, blood lipid profile, etc.), as well as biomarkers associated with CVD risk [37], including markers of inflammation (e.g., CRP & vascular cellular adhesion molecule-1 [VCAM-1]), oxidative stress (e.g., thiobarbituric acid reactive substances [TBARS] & superoxide), and antioxidant status. Individual assays will be performed via enzyme-linked immunosorbent assay kits. Reactive oxygen species will be measured using electron paramagnetic resonance spectroscopy and superoxide fluorescence via peripheral blood mononuclear cells as previously described [38].

*Cerebral vascular function/health* will be measured utilizing trans-cranial Doppler ultrasound assessment of blood velocity in the middle cerebral artery (MCAv_mean_) and Doppler ultrasound measures of blood flow in the extracranial arteries (e.g., internal carotid artery [ICA]) during a hypercapnic challenge induced by breathing 6% Carbon dioxide. Cerebral function/health will be defined as the % increase and slope of the response in MCAv_mean_, ICA_flow_, and ICA or MCA conductance from baseline during hypercapnia. This methodological approach is routinely performed in our laboratory [39, 40]. Importantly, this is predictive of and a contributor to various neurocognitive conditions and cerebral vascular diseases [41, 42].

*Peripheral vascular function/health* will be determined by several commonly utilized approaches. Macrovascular function will be assessed as brachial artery vasodilation following a period of suprasystolic cuff occlusion (i.e., flow-mediated vasodilation). Microvascular function will be assessed as the % change in blood velocity from baseline following cuff release. Large elastic artery health will be assessed as carotid artery intima-media thickness as well as central and peripheral artery ß-stiffness, arterial compliance, and pulse wave velocity utilizing Doppler ultrasound (GE P5) and applanation tonometry (SphygmoCor® CPV Pulse Wave Velocity System). This is critical as impairments in these variables contribute to cerebral vascular dysfunction as well as other forms of CVD [43, 44].

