### Other measures

*Neighborhood environment (SDOH)* We will use the geographic information system tool, PolicyMap, to extract neighborhood-level built environment and social environment characteristics based on participants’ home addresses. We will extract neighborhood-level (e.g., at zip code-level or census track-level) social environment characteristics, including demographic indicators such as racial composition, diversity index (i.e., probability that two individuals chosen at random would be of different races/ethnicities), segregation (Theil index); neighborhood income and poverty, education attainment, employment and unemployment, and crime rate. We will also extract built environment characteristics such as park density, supermarket density, and fast-food restaurant density.

*Covariates* We will ask participants to complete a one-time online survey to assess their demographic information (e.g., age, education level, marital status, employment status, and household income), health literacy, past exposures to lifetime discrimination, and usual diet pattern. These variables will be used as covariates in our statistical models, as needed, and will be helpful in comparing our findings with previous studies and other larger population cohorts.

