### Statistical considerations

Multilevel linear mixed-effect models will be used to account for repeated measures (for daily behaviors and daily experience) within an individual. We will separate the between-person and within-person effects by partitioning the variance. **Aim 1**: The daily experience predictors include (1) racial discrimination (i.e., daily EOD and GRMS score), (2) mood/affective states (i.e., daily average of positive and negative affect), (3) daily stress (i.e., daily average of perceived stress and diurnal cortisol rhythm such as total cortisol output, cortisol awakening response, diurnal cortisol slope). The daily behavior outcome variables include total daily moderate-to-vigorous physical activity minutes, total sedentary minutes, and sleep variables (i.e., SOL, WASO, TST). We will link the predictor and outcome at the day-level so that the acute impact of daily experience on behaviors can be examined. **Aim 2**: Outcome variables are indicators of cardiovascular health from lab-based measurements. We will first test the direct independent effects of daily behaviors on cardiovascular health outcomes using the mixed-effect models. Next, we will add the single-level and cross-level interaction terms to each multilevel mixed-effect model to test the moderation effects of daily experience. **Aim 3**: We will test the direct independent effects of neighborhood-level characteristics (predictors) on daily behaviors and daily experience (outcome variables) using the mixed-effect models. All tests of the hypotheses will be two-sided and an alpha level of 0.05. All analyses will be performed using SAS 9.4.

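### The corticosteroid exclusion is tied to asthma, so it largely repeats the respiratory exclusion and leaves other oral or inhaled steroid use unscreened and unrecorded; the likely bias is small

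*Protocol article*

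**What the plan says.** All the relevant exclusions stand in one sentence of the protocol article, under Participants recruitment and eligibility.

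- Diseases: "diagnosed hypertension, cardiovascular, respiratory, metabolic, and/or neurological disorders".
- Medications: "currently taking medications for thyroid function or psychological conditions such as depression, anxiety, and mood disorders".
- Steroids: "current use of oral or inhalant corticosteroids for asthma".

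The sentence also excludes functional limitations or health issues that preclude physical activity.

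The variables that a steroid could affect appear elsewhere in the article. The abstract states: "Saliva samples will be self-collected to assess cortisol level as a biomarker of psychological stress". Statistical considerations lists, among the Aim 1 daily-stress predictors, "diurnal cortisol rhythm such as total cortisol output, cortisol awakening response, diurnal cortisol slope". Lab-based assessments names CRP and VCAM-1 as inflammation markers, and the Introduction places systemic inflammation among the Aim 2 outcomes. The covariates under Other measures are demographic items plus "health literacy, past exposures to lifetime discrimination, and usual diet pattern". Medication use is not among them.

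**The concern.** Whether a corticosteroid disturbs salivary cortisol or an inflammation marker depends on the drug, route and dose, not on the diagnosis for which it was prescribed. A rule tied to one diagnosis misses the same exposure under another. Here the chosen diagnosis is also one that the disease list already removes, so the clause screens out few women whom the list would not.

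The women left unscreened are users with, for example, an allergic, skin, bowel, joint or autoimmune condition. Cortisol is to be read as psychological stress, and in a user it may partly reflect treatment. Her CRP and VCAM-1 may reflect treatment or the underlying disease. Because cortisol counts as part of daily experience, which is the Aim 2 moderator, such a woman can be displaced on both sides of an Aim 2 model. With no record of use, the analyst could neither adjust for it nor set her values aside.

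That corticosteroids can alter these markers is general pharmacology and is not stated in the article, although the presence of a steroid exclusion suggests that its authors had the problem in mind.

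**Working it through.** The plan gives no figure on this point, so there is nothing to reproduce. The check is a reading of the criteria, followed by arithmetic for scale.

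**1. Who is removed, on a literal reading**

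| Woman | Respiratory exclusion | Steroid exclusion |
|---|---|---|
| Diagnosed asthma, on steroids | excluded | excluded |
| Diagnosed asthma, no steroids | excluded | not reached |
| Treated for asthma, no diagnosis reported | not reached | excluded |
| Oral steroid for a condition outside the listed groups | not reached | not reached |

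Only the third row is added by the steroid clause. The fourth row is the gap.

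**2. What the screening counts show**

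By May 2024, 63 women had been screened and 27 were eligible, so 63 − 27 = 36 were not. Stated reasons cover 15 (medication) + 12 (medical conditions) + 4 (smoking) = 31, leaving 36 − 31 = 5 without one. The 15 are not split by drug, so the number removed by the steroid clause alone cannot be derived.

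**3. How many users might be enrolled**

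The article gives no prevalence. For an assumed prevalence π of corticosteroid use for other indications among otherwise eligible women, the expected number in 80 is 80π, and P(at least one) = 1 − (1 − π)^80.

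| π (assumed) | Expected users | P(at least one) |
|---|---|---|
| 0.5% | 0.4 | 0.33 |
| 1% | 0.8 | 0.55 |
| 2% | 1.6 | 0.80 |
| 3% | 2.4 | 0.91 |
| 5% | 4.0 | 0.98 |

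**4. Induced between-woman correlation**

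Let m of 80 women be users and p = m/80. Suppose use shifts cortisol by d1 and the outcome by d2, in SD units of non-users, with no association between the two otherwise. Then

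r = p(1−p)·d1·d2 / √[(1 + p(1−p)·d1²)(1 + p(1−p)·d2²)].

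Assumed: d1 = 2; d2 = 0.5 or 1.

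- m = 2: p(1−p) = 0.0244. With d2 = 0.5, r = 0.0244/√(1.0975 × 1.0061) = 0.023. With d2 = 1, r = 0.0488/√(1.0975 × 1.0244) = 0.046.
- m = 4: p(1−p) = 0.0475. With d2 = 0.5, r = 0.0475/√(1.19 × 1.0119) = 0.043. With d2 = 1, r = 0.095/√(1.19 × 1.0475) = 0.085.
- m = 8: p(1−p) = 0.09. With d2 = 0.5, r = 0.09/√(1.36 × 1.0225) = 0.076. With d2 = 1, r = 0.18/√(1.36 × 1.09) = 0.148.

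**5. Against sampling error**

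The standard error of a null correlation with n = 80 is about 1/√79 = 0.11, and |r| must exceed about 0.22 for two-sided p < 0.05. Two to four users give 0.02 to 0.09, under one standard error. Eight users, 10% of the sample and above the range assumed in step 3, reach at most 0.15.

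**The case against.** The strongest reply is that the effect is negligible. Step 5 bears this out for the likely number of users, and it sets the tone of the verdict.

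A second reply is that Aim 1 is framed at the intrapersonal level and its models separate within-person from between-person effects. Steady steroid use over the three saliva days is a shift at the level of the woman. It goes into the between-person term and would mainly weaken a within-person cortisol association, not create one. This stands, although the between-person effects are to be estimated too. Likewise, the main Aim 2 test relates behaviors to outcomes, with daily experience as moderator. The correlation above is not a calculation for that interaction, and CRP and VCAM-1 are two markers in a wide panel.

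A reader might infer two stronger things that the article does not support.

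- *That the steroid and respiratory criteria contradict each other.* They overlap. Read literally, diagnosed asthma without steroids is excluded, and a separate drug item can catch a woman who did not report a respiratory diagnosis. Only if the investigators meant to admit asthma without steroids would the two conflict, and the article does not say so.
- *That every other steroid user passes.* Some are caught by the metabolic, neurological or other respiratory exclusions, by the thyroid-medication rule, or by the criterion on health issues that preclude physical activity.

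Finally, the list is introduced as what the criteria include, and an operating procedure covering recruitment exists but is not shown. That leaves room for unseen detail, but nothing in the article widens a steroid rule that it states with a specific indication.

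**Conclusion.** The point holds in a limited form. As written, the steroid exclusion nearly duplicates the respiratory one, some oral or inhaled users with other conditions remain eligible, and no listed covariate identifies them. Their cortisol, CRP and VCAM-1 may be altered by drug or disease, to a degree that depends on dose and route.

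The size is small: an induced between-woman correlation of about 0.02 to 0.09 for two to four users. This rests on the assumed number of users, the assumed shifts of 2 SD and 0.5 to 1 SD, and a simple two-group model; none of these comes from the article. It does not threaten the study as a whole, and it does not show that the within-person Aim 1 results would be spurious. It is worth correcting because it lies in a stated rule, touches variables named in two aims, and is cheap to put right while enrollment continues (expected to finish around October 2025).

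**What to change.** 1. Delete the words *for asthma*, so that current oral or inhaled corticosteroid use excludes whatever the indication.
2. Reconcile the steroid and respiratory criteria by stating whether a woman with asthma who takes no steroids is eligible.
3. Record corticosteroid use by any route, and diagnosed inflammatory disease, for all participants. The exit survey can carry this for women still in the study; those who have finished need re-contact.
4. Pre-state a sensitivity analysis of the cortisol and inflammation models without users.

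The cost is an IRB amendment, one or two extra questions, some re-contact and a few more screen failures. The number of extra failures cannot be estimated from the article, and 36 of 63 screened women (57%) were already ineligible. For that reason wider exclusions, such as intranasal or injected routes, a look-back window, or all chronic inflammatory disease, are optional trade-offs outside the core repair. If the sponsor prefers not to narrow eligibility, steps 3 and 4 alone would let the effect of any users on the results be examined.
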